### Sample size calculation

The number of working hours lost due to sick leave by musculoskeletal injuries (M Group International Classification of Diseases, ICD-10) was used to estimate the sample size. The average time lost during the last three months in companies that the study observed was approximately 1,100 hours. The authors assume that interventions will enable a reduction of this number by 10%, that is, the groups will have a difference of 100 lost working hours, with a standard deviation of 250 hours. A statistical power of 80%, an alpha of 5%, and a possible sample loss of up to 15% is considered. Therefore, 116 participants are needed per group, or 232 in total. But, in this study the calculation of sample size was made by clusters and considered the number of production sectors included. The clusters number was four sectors (n = 957). The intervention group has 504 workers selected from Finishing Socks and Finishing Underwear departments, and the control group is 453selected from Sewing Socks and Sewing Underwear departments (Figure 1).

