### Randomization

Randomization was performed at the group level (departments/productive sectors), in order to avoid contamination from workers allocated in the intervention to those in the control group. The productive sectors included in the study were pre-stratified by the level of exposure to risk factors for musculoskeletal pain and disorders. Sectors with similar demands were grouped and randomly divided between intervention and control groups. Using a computer-generated randomization (http://www.randomizer.org) with random numbers to define groups, the randomization was performed by an independent researcher who was not involved in recruitment and assessment. Sealed envelopes will be used. The randomization was performed before baseline measurements.

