### Assessment instruments and outcomes

Although the intervention is applied to the production sectors, the outcomes are on an individual level, since they reflect aspects of the health of workers. Data regarding outcome measures will be assessed at baseline and after 3, 6, and 12 months, except for information relating to removal for sick leave, which will be recorded daily. After a period of 12 months, the sector that had received only ergonomic guidelines will receive job rotation considering the hypothesis of this study in relation to its effectiveness. Both groups of workers will be monitored in a longitudinal study in subsequent months and compared to other workers identified within the criteria for risk analysis for 24 months.

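### Both Finishing departments are in the intervention arm and both Sewing departments in the control arm, so the planned group difference mixes the rotation effect with any finishing-sewing difference

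*Protocol article*

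**What the plan says.** All references are to the protocol article.

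- **Randomization.** Departments are the units: "Randomization was performed at the group level (departments/productive sectors"). They were "pre-stratified by the level of exposure to risk factors for musculoskeletal pain and disorders", and "Sectors with similar demands were grouped and randomly divided between intervention and control groups". The strata are not named.
- **Sample size calculation.** "The clusters number was four sectors (n = 957"). This section also lists the arms: "The intervention group has 504 workers selected from Finishing Socks and Finishing Underwear departments, and the control group is 453selected from Sewing Socks". The other control department is Sewing Underwear.
- **Job rotation.** Exposure level, posture, main physical demand and loaded body region are the criteria for building the rotation. The tasks listed under Figure 2 are shaping, pairing, stamping, packaging, reviewing and the like. None is named as sewing.
- **Statistical analysis.** The difference between groups and its confidence interval come from linear mixed models, by intention to treat. No step for type of process is stated.
- **Assessment instruments and outcomes.** Sick leave is recorded daily. "After a period of 12 months, the sector that had received only ergonomic guidelines will receive job rotation".

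**The concern.** With four clusters, two per arm, each arm contains only one type of process. Finishing and sewing are different jobs. On the protocol's own premise, posture, physical demand and loaded body region drive musculoskeletal risk, so the two kinds of department could differ in sick leave before any rotation starts. A plain comparison of the arms would credit such a difference to rotation. A gap favouring Finishing could look like a benefit, and a gap favouring Sewing could hide one. Recruiting more workers in the same four departments does not help, because the overlap is between departments. At stake is whether the result, positive or null, can be attributed to job rotation, which is the question the trial asks.

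**Working it through.** **1. The plan's own sample size.** Inputs from Sample size calculation: difference 100 h, SD 250 h, power 80%, alpha 5% (two-sided assumed), loss 15%.

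n per arm = 2 x (1.960 + 0.842)^2 x (250/100)^2 = 98.1, rounded up to 99. Allowing for loss, 99/0.85 = 116.5, rounded up to 117; rounding only at the end, 98.1/0.85 = 115.4, rounded up to 116. The stated 116 is reproduced. It assumes individual randomization and has no bearing on the overlap of arm and process.

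**2. Can the two effects be separated at one time point?** Order the departments as Finishing Socks (FS), Finishing Underwear (FU), Sewing Socks (SS), Sewing Underwear (SU).

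- Arm (1 = intervention): 1, 1, 0, 0
- Process (1 = finishing): 1, 1, 0, 0
- Product (1 = socks): 1, 0, 1, 0

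Arm and process are the same column, so intercept, arm and process together have rank 2 of 3. Each arm has one socks and one underwear department, so product is balanced. For an allocation such as FS + SU versus FU + SS, the arm column is 1, 0, 0, 1 and the rank is 3 of 3.

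**3. What each contrast estimates.** Let F and S be the pre-trial mean lost hours in Finishing and Sewing, tF and tS their changes over time without rotation, and R the rotation effect in Finishing.

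- Follow-up only: (F + tF + R) - (S + tS) = R + (F - S) + (tF - tS)
- Change from each department's own pre-trial level: (tF + R) - tS = R + (tF - tS)

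The change contrast removes the stable gap F - S. It leaves tF - tS, and R remains an effect in Finishing only.

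**4. Size.** The planned effect is 100/1,100 = 9.1% of current lost hours (the article rounds this to 10%). The gap F - S is not given, so these values are assumptions:

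| Assumed gap | Share of 1,100 h | Share of planned effect |
|---|---|---|
| 25 h | 2.3% | 25% |
| 50 h | 4.5% | 50% |
| 100 h | 9.1% | 100% |

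**5. Was the allocation possible under the stated method?** There are six 2:2 splits: two align arm with process, two align arm with product (FS + SS, FU + SU), and two balance both (FS + SU, FU + SS).

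| How sectors might have been grouped | Draws aligning arm with process |
|---|---|
| Paired by process | 0 of 4 |
| Paired by product | 2 of 4 |
| All four in one exposure stratum | 2 of 6 |
| Like sectors grouped, whole groups assigned | all |

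Only pairing by process rules out the reported allocation. The article does not say which grouping applied.

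**The case against.** **Chance imbalance is part of randomization.** This is fair as far as it goes. Strata were formed by exposure level, and if all four sectors fell in one stratum this allocation is an ordinary draw. A reader might infer that the stated method was broken, and the article does not support that. However, saying that grouped sectors had similar demands does not make the arms comparable when the groups are not named and no department figures are given.

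**The departments may not differ.** This also stands. A reader might infer that sick-leave rates are known to differ between finishing and sewing. The article gives no rate and no Quick Exposure Check (QEC) or Rapid Entire Body Assessment (REBA) result by department, so any gap is an assumption.

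**A longitudinal mixed model can handle it.** In part. It is tempting to say that no comparison of these arms can ever remove the problem, but step 3 shows that a change-from-baseline contrast removes a stable gap. The full plan may contain such a contrast. The article states only a difference between groups, and for the primary outcome it names no pre-trial hours as baseline.

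**Simply redraw within process type.** This is weaker than it looks. Of the four draws within process, two (FS + SS, FU + SU) put all socks in one arm and all underwear in the other, so product would then coincide with arm. Randomization has already been done, and the rotation is already designed around finishing-type tasks.

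**Conclusion.** The point holds in this form: arm and process type coincide completely, and the between-group difference as written estimates rotation plus any finishing-sewing difference. This follows from the stated allocation and needs no assumption. The size of the bias is unknown; under the assumption of a 100-hour pre-existing gap (9.1% of 1,100) it equals the whole planned effect, in either direction.

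The evidence does not establish a breach of the randomization procedure, a known baseline difference, or a problem beyond any analysis. What no analysis of the first 12 months can remove is narrower: trends specific to one process, and the possibility that rotation works differently in sewing than in finishing. The weak between-cluster inference from two departments per arm is a separate issue that the change below does not cure.

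**What to change.** 1. **Primary contrast.** Define it as the difference between arms in change from each department's own pre-trial HR musculoskeletal hours, using a pre-trial period as long as follow-up where records allow. The sample size section shows that at least three months of such hours were obtained. It does not say whether they were split by department.
2. **Baseline reporting.** Tabulate pre-trial sick leave and QEC/REBA exposure for each of the four departments.
3. **Strata.** State under Randomization and Sample size calculation how the strata were formed and which departments fell in each.
4. **Conclusion.** Limit it to rotation in finishing departments, with sewing departments as a non-equivalent comparison, and name process-specific trends and effect modification as remaining limits.
5. **Supportive evidence.** The before/after contrast in Sewing when rotation starts there at 12 months can be pre-specified as supportive only, because it is uncontrolled. Clarify whether the 24 months of later monitoring are a total or an addition.
6. **Redraw.** Drop the idea, or consider it only if rotation has not started. In that case restrict it to the split that balances both factors (Finishing Socks + Sewing Underwear versus Finishing Underwear + Sewing Socks), with an independent draw deciding which pair receives rotation.

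Items 1 to 5 cost one extra HR extract, some added wording and a more modest causal claim. Item 6 is not cheap: it needs a new draw after the result of the existing one is known, and a rotation plan for a Sewing department earlier than intended.

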**Figure 1 F1:**
[figure not shown]
Study flow diagram.

### Randomization

Randomization was performed at the group level (departments/productive sectors), in order to avoid contamination from workers allocated in the intervention to those in the control group. The productive sectors included in the study were pre-stratified by the level of exposure to risk factors for musculoskeletal pain and disorders. Sectors with similar demands were grouped and randomly divided between intervention and control groups. Using a computer-generated randomization (http://www.randomizer.org) with random numbers to define groups, the randomization was performed by an independent researcher who was not involved in recruitment and assessment. Sealed envelopes will be used. The randomization was performed before baseline measurements.

### Blinding

Obviously, the nature of the intervention used in this study made it impossible to blind workers and ergonomists. However, the workers’ interview researcher will be blind to the study design and the group assignment. To test blinding, after assessment of outcomes, the worker’s assessment researcher will note his opinion as to the type of intervention received by workers. Moreover, all workers in both groups will receive ergonomic guidelines, used as a placebo intervention.

### Study groups

#### ***Control group***

Workers allocated in the control group will be invited to attend training with ergonomic guidelines, taught by a physiotherapist/ergonomist. The training will be held on a single day over 4 hours, with lectures on: ergonomic risk factors and their influence on the development of musculoskeletal symptoms, improvements and adaptations for workstations, work postures, and preventive exercise [15]. Participants in the intervention group will receive the same information.

#### ***Intervention group***

Workers allocated in intervention sectors will receive the same ergonomic guidelines as the control group. In addition, they will realize job rotation, as described below.

### Intervention

#### ***Job rotation***

The job rotation is proposed in order to modify exposure, so that workers will perform tasks alternating between low, moderate, and high risk for musculoskeletal pain and disorders and exposure to risk for injury to different body regions. Therefore, an ergonomic analysis will indicate, based on the main posture adopted to carry out the task, the body regions of higher overload level and intensity of exposure. The autonomy of the work (techniques and work rate) and the use of machines and tools will also be evaluated. The level of exposure to risk of musculoskeletal pain and disorders will be assessed by Quick Exposure Check (QEC) [16,17] and Rapid Entire Body Assessment (REBA) [18]. These methods enable the characterization of worker exposure to the task because they assess the main risk factors for musculoskeletal disorders (frequency of movements and postures performed by spine and upper limbs, amount of weight handled, time to perform the task, manual force, visual demands of the activity, presence of vibration, work pace, and stress) [16,17].

The structure of the job rotation will be proposed from the results obtained by ergonomic assessment, according to the following priority criteria: (1) level of exposure intensity (low, moderate, high, or very high), (2) posture predominantly adopted for conducting task (sitting, kneeling, standing, walking), (3) the main physical demand (material handling, repetition of movements, static posture), and (4) body regions of higher overhead (shoulders, elbows, wrists, hands, spine) (Table 1). Tasks that have similarity of these criteria will be grouped to then be alternated, so that: (1) tasks with exposure level will be low or moderate risk tasks alternated with high and very high, (2) tasks that require a predominantly standing posture will alternate with tasks that require a sitting posture, (3) handling tasks will be alternated with tasks requiring repetition of movements, and (4) the tasks alternate body regions of higher overhead (Figure 2). The completion of the rotation will take place at intervals of 2 hours. It is estimated that this time is compatible with a lower lactic acid [19].

**Table 1 T1:** Summarized description of the job rotation definition

**Step**	**Definition**	**Description**
1	**Ergonomic work analysis**	Evaluate the main demand of work posture adopted in the task, movements per body region (amplitude and frequency), autonomy, work rate, percentage of occupation in work cycles
2	**Ergonomic exposure risk level assessment**	Classify the activity exposure level ergonomic (low, moderate, high and very high) by two observational protocols: Quick Exposure Check (QEC) and Rapid Entire Body Assessment (REBA)
3	**Job rotation definition**	Propose the structure of job rotation in accordance with the following priority criteria: (1) the level of exposure intensity (low, moderate, high or very high), (2) predominantly stance taken by the completion task (sitting, kneeling, standing, walking), (3) the main physical demand (material handling, repetition of movements, static posture), (4) body regions of higher overhead (shoulders, elbows, wrists, hands, spine), (5) production’s specificities

**Figure 2 F2:**
[figure not shown]
**Job rotation design.** Group A (operate Alome machine; Firsan- shaping socks; separation of product’s color and size; stamping; Tecma machine packaging; silicon preparing); Group B (Alome - choice of pair of socks; operate Satellite machine; operate Sealing machine; fix fast pin; automatic packaging); Group C (Firsan- choice of pair of socks; Satellite packing socks; Alome – socks review; manual packaging; operate Autotex machine; application of silicon; seamless products review).

### Assessment instruments and outcomes

Although the intervention is applied to the production sectors, the outcomes are on an individual level, since they reflect aspects of the health of workers. Data regarding outcome measures will be assessed at baseline and after 3, 6, and 12 months, except for information relating to removal for sick leave, which will be recorded daily. After a period of 12 months, the sector that had received only ergonomic guidelines will receive job rotation considering the hypothesis of this study in relation to its effectiveness. Both groups of workers will be monitored in a longitudinal study in subsequent months and compared to other workers identified within the criteria for risk analysis for 24 months.

### Socio-demographic

At baseline, socio-demographics (age, sex, level of education, length of service in the company and the current role, working days per week, and hours of work per week, among others) will be assessed using a questionnaire developed by the researchers of this study.

### Primary outcome measure

#### ***Absence from work due to sick leave***

In this study, we will use the sick leave for sick leave due to illness of the musculoskeletal system and connective tissue as a primary outcome measure. This outcome will be measured by the number of working hours lost due to the removal of a symptom or disease of the musculoskeletal system and connective tissue. These data will be obtained from records of medical certificates validated by the Human Resources department (HR) of each industry. Information regarding the clinical diagnosis and body region will also be collected using the specific codes of the International Classification of Diseases, 10th revision (ICD-10).

### Secondary outcome measure

#### ***Musculoskeletal symptoms***

The occurrence of musculoskeletal symptoms (pain, tingling, or numbness) will be assessed using the Nordic Musculoskeletal Questionnaire (QNSO) [20]. The respondents will answer simple questions (yes or no) in relation to musculoskeletal symptoms they have experienced in the past 12 months and/or in the past seven days, as well as regarding the occurrence of disability and demand for health aid professionals in the last 12 months due to these symptoms. The intensity of the pain will be assessed by the Verbal Numerical Pain Scale [21]. It is an 11-point scale, where 0 means "no pain" and 10 means "worst possible pain."

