**Methods/Design:**

A cluster randomized controlled trial will be used to investigate the effectiveness of job rotation to prevent musculoskeletal disorders in industrial workers. The randomized cluster was based in characteristics of production sectors. A total cluster will be 4 sectors, and 957 workers will be recruited from a textile industry and randomly allocated into intervention or control groups. Both groups will receive training on ergonomics guidelines. In addition, the intervention group will perform job rotation, switching between tasks with low, moderate, and high risk for musculoskeletal complaints. The primary outcome will be the number of working hours lost due to sick leave by musculoskeletal injuries recorded in employee administrative data bases. Secondary outcomes measured via survey include: body parts with musculoskeletal pain, the intensity of this pain, physical workload, fatigue, general health status, physical activity level, and work productivity. Secondary outcome measures will be assessed at baseline and after 3, 6, 9, and 12 months. The cost-effectiveness analysis will be performed from the societal and company perspective.

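### The Nordic questionnaire's 12-month items are scheduled at interim visits where much of the recall period precedes job rotation, so those comparisons are diluted

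*Protocol article*

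**What the plan says.** The Musculoskeletal symptoms section describes yes/no questions with two recall windows for symptoms: "musculoskeletal symptoms they have experienced in the past 12 months and/or in the past seven days". The same sentence adds the "occurrence of disability and demand for health aid professionals in the last 12 months due to these symptoms". These two items have no shorter window. Pain intensity is rated on a separate 0-10 scale with no stated recall period.

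The section Assessment instruments and outcomes sets the timing: "Data regarding outcome measures will be assessed at baseline and after 3, 6, and 12 months, except for information relating to removal for sick leave". Only sick leave is exempted. The Abstract gives a different schedule: "Secondary outcome measures will be assessed at baseline and after 3, 6, 9, and 12 months". Nothing limits the 12-month items to baseline and month 12, shortens their recall at interim visits, or says which symptom window is the outcome there.

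The controlled comparison ends at one year: "After a period of 12 months, the sector that had received only ergonomic guidelines will receive job rotation". The Productivity section, by contrast, uses a three-month recall.

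**The concern.** A 12-month yes/no question suits baseline and the one-year visit. Asked at month 3 or 6, it mostly or half describes the time before rotation began. A worker who had symptoms, disability or a consultation in that earlier period and none since must truthfully answer yes, in either arm. The item cannot record that improvement until the earlier period has passed out of the window.

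Two things are at stake. Interim comparisons on these items understate any effect. And because the pre-rotation share shrinks from visit to visit, an effect that is immediate and constant would look gradual and could be read as delayed. For symptoms, the 7-day answers offer a way out at the analysis stage. For disability and care-seeking they do not: if those are asked as written, no later analysis can separate events before and after the start of rotation at the interim visits.

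**Working it through.** The article gives no figure for the Nordic outcomes, so there is none to reproduce. The sample size concerns sick-leave hours and does not bear on this point.

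**Step 1: share of the window before rotation.** Inputs are the 12-month recall (Musculoskeletal symptoms), visits at 3, 6 and 12 months (Assessment instruments and outcomes) and at 9 months (Abstract only). Assumption: rotation starts at baseline. The share at month *t* is (12 - *t*)/12.

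| Visit | Calculation | 12-month items | 7-day item |
|---|---|---|---|
| Month 3 | 9/12 | 75% | 0% |
| Month 6 | 6/12 | 50% | 0% |
| Month 9 (Abstract only) | 3/12 | 25% | 0% |
| Month 12 | 0/12 | 0% | 0% |

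If rotation starts *s* months after baseline, the share on the 12-month items becomes (12 - *t* + *s*)/12, so a later start raises each of those shares.

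**Step 2: what this does to the group difference.** The article gives no prevalence or expected effect for these items, so the following is illustration. Assume a 12-month control prevalence *p*, a constant onset rate L = -ln(1 - *p*) per 12 months, the same rate in both arms before rotation, and a rate multiplied by *h* under rotation. Then at month *t*:

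- control: *p*
- intervention: 1 - exp(-L x [(12 - *t*) + *h* x *t*]/12)

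With *p* = 0.60 and *h* = 0.70, L = -ln(0.4) = 0.916:

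- Month 3: 1 - exp(-0.916 x 0.925) = 0.572, a difference of 2.8 points.
- Month 6: 1 - exp(-0.916 x 0.85) = 0.541, a difference of 5.9 points.
- Month 12: 1 - exp(-0.916 x 0.70) = 0.473, a difference of 12.7 points.

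The true effect is identical throughout; only the window changes. A 3-month recall at month 3 would give 0.205 against 0.148, or 5.7 points, about twice the 2.8 points from the 12-month item.

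**Step 3: sensitivity.** With *p* at 30%, 50% and 70% and rate reductions of 20%, 30% and 40%, the difference as a fraction of its month-12 size is 21-24% at month 3, 44-49% at month 6 and 70-74% at month 9. The relative dilution follows the post-rotation share of the window (25%, 50%, 75%) and depends little on the inputs. The absolute differences do depend on them.

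**Step 4: the 7-day item under the same model.** Seven days is 7/365 of a year. Control: 1 - exp(-0.916 x 7/365) = 1.74%. Intervention: 1 - exp(-0.7 x 0.916 x 7/365) = 1.22%. The difference is about 0.5 points. Divided by the square root of the summed binomial variances, it is 0.030, against 0.041 for the 12-month item at month 3. The item is free of pre-rotation recall, but this model does not show it to be more sensitive. An onset-only model also represents persistent pain poorly, so neither this figure nor the absolute differences in step 2 should be taken as forecasts.

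**The case against.** The strongest reply is that the section lists what the questionnaire collects, not what is analysed at each visit. A 7-day item is already there, and naming the item for each visit is detail that a condensed article may leave to the full protocol or analysis plan. These are also secondary outcomes, and the Abstract's list of secondary outcomes names neither disability nor care-seeking.

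For symptoms, much of this stands: clean data will exist and only the rule is open. It does not dispose of disability and care-seeking. The article itself fixes both their 12-month window and the schedule, and the problem arises at data collection.

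Three stronger readings are tempting, and the document supports none of them.

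- A reader might infer that all early symptom comparisons are diluted. The 7-day item is not affected, and no recall period is stated for pain intensity.
- A reader might infer that the recall window alone would produce a contrast that rises over time. It would not: under the model above, no effect (*h* = 1) gives a zero difference at every visit. The window only reshapes the time course of a real effect.
- A reader might infer that overlapping windows count the same episode several times. The items are yes/no and count no episodes. One episode can support a yes at successive visits, but the linear mixed models in Statistical analysis can allow for correlation between a worker's repeated answers. That does not remove the dilution.

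**Conclusion.** The point holds for the 12-month items at the interim visits, and most firmly for disability and care-seeking. The pre-rotation share is 75% at month 3, 50% at month 6 and, if the Abstract's schedule applies, 25% at month 9. These shares rest only on rotation starting at baseline. The bias toward no difference also assumes similar pre-rotation levels in the two arms; if the sectors differed beforehand, the interim contrast would be pulled toward that earlier difference instead. The loss to roughly a quarter and a half of the month-12 contrast rests on the assumed constant-onset model.

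The consequence is limited. The month-12 window is clean under the same start assumption, and the primary outcome is recorded daily and is untouched. The correction is worth making because it is nearly free before data collection and, for two of the items, unavailable afterwards.

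**What to change.** Add a short rule to the Musculoskeletal symptoms section:

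1. The 12-month symptom, disability and care-seeking items are analysed only at baseline and month 12.
2. At interim visits (3 and 6 months, and 9 if kept), the 7-day item is the symptom outcome, adjusted for its baseline value.
3. At interim visits, disability and care-seeking are asked for the time since the last interview.
4. This rule replaces *and/or* in the description of the symptom windows.

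The cost is a few sentences. The 7-day option needs no new data, though a one-week window may yield few positive answers. The reworded recall departs slightly from the standard form, and its interim answers cannot be compared directly with the 12-month baseline answers; they support comparison between arms at the same visit. The article already uses a three-month recall for productivity, so a shorter recall is practicable in this survey.
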